In case of cerebellar dysfunction resulting from MS-related pathological changes, performing precise movement might be impossible. In fact, altered hand dexterity could affect 76% of MS patients, is associated with the deterioration of the overall upper limb activity and disuse, increases the need for more assistance and the perceived difficulties with activities of daily living [25,26,27]. Facing this source of disability, the available medical treatments showed very limited benefits in improving hand dexterity. Noninvasive brain stimulation (NIBS) techniques seem appealing tools to treat various neuropsychiatric complaints, including those encountered in patients with MS [28]. Transcranial direct current stimulation (tDCS) is a relatively new NIBS technique with a good safety profile, easy implementation, good patients’ tolerance, and little or no adverse effects [29,30,31,32,33,34,35]. It could modify spontaneous neuronal excitability and activity by tonic depolarization (anodal tDCS) or hyperpolarization (cathodal tDCS) of the neuronal resting membrane potential [36,37]. To date, tDCS effects on hand dexterity have not been explored in MS [38]. The main objective of this work is to evaluate the effects in question. Stimulating the motor cortex, or removing the cerebellar inhibition over it, can be beneficial in improving dexterity in MS patients. Therefore, in this work, we thought of activating (anodal tDCS) the primary motor cortex (M1) contralateral to the most affected hand or inhibiting (cathodal tDCS) the cerebellar cortex (i.e., Purkinje cells) aiming to facilitate motor output.

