### 2.3. Sample Size, Randomization and Blinding Effectiveness

In the absence of published data on this topic, the statistical outcomes of this study can serve in understanding and guiding the therapies of altered dexterity in MS patients. Previous tDCS studies addressing dexterity in stroke patients adopted sample sizes between 10 and 19 and yielded statistical significance [59,60].

In the absence of sham-controlled studies on this matter, sample size calculation was performed using the G*Power Software (version 3.1.9.6 [61]). A 2 × 3 within-subjects repeated measures analysis of variance was considered, with the factor time (before and after each stimulation condition) and the factor stimulation condition (active cathodal cerebellar, active anodal motor vs. sham). Considering the predicted medium effect size (f = 0.25) and adopting a two-tailed significant difference of α = 0.05 and an estimated power of 80%, the sample size estimate is 36. Taking into consideration a dropout rate of up to 25%, a sample of 45 patients will be sufficient to observe significant effects. *N* = 48 was adopted to be able to counterbalance the order of conditions as will be explained below.

Randomization will be performed by a researcher who will not be in contact with patients. In the first step, six different sets of blocks will be assigned, and each contains four patients: (active cathodal cerebellar, sham, active anodal motor), set B (active cathodal cerebellar, active anodal motor, sham), set C (sham, active cathodal cerebellar, active anodal motor), set D (sham, active anodal motor, active cathodal cerebellar), set E (active anodal motor, sham, active cathodal cerebellar), and set F (active anodal motor, active cathodal cerebellar, sham). In the second step, each set will be split into two subsets according to the sham setup, so that two patients per set will receive sham over the motor cortex (setup similar to active condition), and the other ones will receive sham over the cerebellum (setup similar to active condition). The flow chart of the protocol is displayed in Figure 2. The evaluators will assess the patients before and after tDCS blocks and will be blind to the stimulation conditions. Patients will be blind to the stimulation condition.

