### 2.9. Statistical Analysis

The statistical analysis will be performed using the SPSS software (IBM Corp. Released 2016. IBM SPSS Statistics for Windows, Version 24.0. Armonk, NY: IBM Corp). The primary and secondary outcomes will be analyzed using the same statistical approach. For all variables, the normality of data distribution will be tested using the Kolmogorov–Smirnov test. The homogeneity of variance will be tested using the Levene’s test. Depending on the data distribution, the scores obtained before and after all tDCS conditions will be compared using the repeated measures analysis of variance (ANOVA) or the Friedman test under six conditions: 2 times (before and after tDCS) × 3 stimulation conditions (anodal motor tDCS, cathodal cerebellar tDCS, and sham). When appropriate, the post hoc Dunn’s test will be applied. Two-tailed p-values less than 0.05 will be considered significant. Data will be presented as the mean ± the standard deviation or the median (1st and 3rd quartiles).

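### Section 2.9 names no test of active change against sham change, and its six-cell Friedman/Dunn branch cannot provide one: it can reject on a before-to-after gain that sham shares

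*Protocol article*

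**What the plan says.** The Introduction poses two efficacy questions, one for each site: "Stimulating the motor cortex, or removing the cerebellar inhibition over it, can be beneficial in improving dexterity in MS patients".

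Section 2.3 sizes the trial on one model: "A 2 × 3 within-subjects repeated measures analysis of variance was considered", whose second factor is "the factor stimulation condition (active cathodal cerebellar, active anodal motor vs. sham". The effect size is given without saying whether it belongs to time, condition or their interaction: "Considering the predicted medium effect size (f = 0.25". The result follows: "adopting a two-tailed significant difference of α = 0.05 and an estimated power of 80%, the sample size estimate is 36".

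Section 2.9 applies the same approach to primary and secondary outcomes. Depending on the distribution, it uses "repeated measures analysis of variance (ANOVA) or the Friedman test under six conditions". The six conditions are the cells "2 times (before and after tDCS) × 3 stimulation conditions (anodal motor tDCS, cathodal cerebellar tDCS, and sham). When appropriate, the post hoc Dunn’s test will" follow. The decision threshold is one sentence: "Two-tailed p-values less than 0.05 will be considered significant". The section does not say which ANOVA term decides, which pairs Dunn's test compares, or what triggers it.

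**The concern.** In a sham-controlled crossover with scores before and after each block, efficacy means that the change under active stimulation exceeds the change under sham. On the ANOVA branch only the interaction addresses this. The time effect is the average gain over all three blocks, sham included. The condition effect averages in the scores taken before stimulation.

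The Friedman branch is worse placed, because it treats the six cells as six unstructured conditions and so contains no interaction at all. A shared gain is plausible: the 9-HPT is taken on D1 and D5 of each of three blocks (Section 2.5), so each patient is assessed six times. The five training trials in Section 2.4.1 may reduce practice effects but do not remove a placebo response.

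At stake is whether a significant result from the analysis as written says anything about stimulation, and whether the two site-specific questions are answered by a rule fixed beforehand.

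**Working it through.** **1. Does the sample size reveal the intended test?** The inputs in Section 2.3 are f = 0.25, alpha 0.05, power 80% and N = 36. Correlation ρ, sphericity ε, number of measurements m and number of groups are not stated, so they are assumed here. For a within-subject factor, noncentrality is λ = f²·N·m·ε/(1−ρ), with degrees of freedom (m−1)ε and (N−groups)(m−1)ε.

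- One group, m = 6, ρ = 0, ε = 1: λ = 0.0625 × 36 × 6 = 13.5, df 5 and 175, power 80.9%. N = 36 is reproduced exactly, as an omnibus test of six cells.
- One group, ρ = 0.5: m = 2 gives 34, m = 3 gives 28, m = 6 gives 19.
- m = 2, ρ = 0.5, with 3 or 6 groups: also 36.

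Several settings reach 36, so the sample size does not identify the powered effect.

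**2. What each test responds to.** Suppose stimulation does nothing and every block has the same gain g. The three before cells then have mean μ and the three after cells μ + g.

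- Time effect: g. Condition effect: 0. Interaction: 0.
- Six-cell Friedman: its null hypothesis is false whenever g is not 0.
- Dunn's test: 6 × 5/2 = 15 pairs. Of these, 3 × 3 = 9 compare a before cell with an after cell and differ by g; the other 6 differ by 0. No pair is a difference of changes.

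**3. Size under a shared gain.** Assumed: 48 patients, normal data, total SD 1, correlation 0.75, g = 0.1 or 0.2 SD, no stimulation effect. The within-patient variance is 0.25, so a block's change has variance 2 × 0.25 = 0.5. The mean of three changes has variance 0.5/3 = 0.167, SD 0.408.

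- Noncentrality of the time test: g × √48/0.408 = 1.70 or 3.39, giving power 38% or 91% (noncentral t, 47 df).
- At least one of three F tests: 1 − (1 − 0.383) × 0.95² = 44%, or 1 − (1 − 0.914) × 0.95² = 92%. Simulation of 20,000 trials gives 44% to 45% and 92%.
- Six-cell Friedman, by simulation: about 18% or 63%.
- Interaction, by simulation: about 5% in both cases.

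**4. Error with no effect of any kind, under three readings of the plan.**

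- Any of the three F tests counts as success: 1 − 0.95³ = 14.3%.
- Two active-versus-sham contrasts, each at 0.05, ungated and unadjusted. Sharing sham gives them correlation 0.5: 9.1%.
- The same two contrasts, run only after a significant interaction: about 4%.

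**5. Power cost of error control.** Under the step 3 variances, active change minus sham change has variance 4 × 0.25 = 1, so an assumed benefit of 0.4 SD is a standardized paired difference of 0.4. Power per contrast falls from 77.5% at 0.05 to 67.6% at 0.025 with 48 patients, and from 64.6% to 52.9% with 36. If both sites are 0.4 SD better than sham, the chance of at least one claim is:

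- 48 patients: about 82% to 83% with Holm, 81% when gated on the interaction, 90% unadjusted.
- 36 patients: about 70% with Holm, 80% unadjusted.

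**The case against.** The natural reading of Section 2.9 is sequential: an omnibus test, then a post hoc procedure designed for multiple comparisons. The trial is sham-controlled, the Abstract defines the primary outcome as a change, and Section 2.3 sets the active conditions against sham. All of this points to time by condition. The threshold sentence sets when a p-value is called significant; it is not a rule for declaring efficacy. The Discussion calls the study exploratory, and an analysis plan that is not shown may list contrasts and adjustments.

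Much of this stands, and it rules out stronger readings that a reader might infer:

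- **A family-wise error of 9% to 14% for this plan.** The 14% requires a main effect to count as success, which the article does not say. The 9% requires ungated, unadjusted contrasts, which it does not describe.
- **The 44% and 92% as false-positive rates.** They are correct detections of a shared gain that was put into the simulation.
- **A significant interaction with neither site differing from sham as an error.** If the sites differ by 0.4 SD with sham midway, this occurs in 19% of simulated trials, but the difference between sites is real.

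The objection does not reach the Friedman branch. That test over six conditions is fixed in the text, and gating Dunn's test on it gives no protection when a shared gain triggers the gate. The pointers towards the interaction do not name it. The exploratory label is offered as the reason for measuring short-term effects only, and the trial still has a primary outcome, 80% power and a significance threshold.

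**Conclusion.** The point holds in this form: the article names no deciding test for the primary outcome, and one of its two analysis branches, followed as written, cannot answer the sham-controlled question. That much follows from the structure of the tests and needs no simulation.

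The size depends on values the documents do not give. The figures of 18% and 63% for Friedman, against about 5% for the interaction, rest on normal data, 48 patients, correlation 0.75 and the chosen shared gains. They show how often a significant result would be uninformative about stimulation. They do not estimate the error rate of an efficacy test, because none is stated. The change should be made before analysis; the finding does not show that the eventual claims would be wrong.

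**What to change.** In Section 2.9, compute each block's change in the 9-HPT (D5 against D1). Base efficacy claims only on two contrasts: motor change minus sham change, and cerebellar change minus sham change. State the error control in advance, either Holm at two-sided 0.05 overall, or the two contrasts tested only after a significant time-by-condition interaction. Either is adequate.

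For non-normal data, replace the six-cell Friedman/Dunn procedure with the matching test on change scores: Friedman over the three changes, or paired signed-rank tests of the two contrasts under the same error control. Report the time and condition main effects, and motor versus cerebellar, as descriptive.

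This takes a few sentences and no new data. The price is power: relative to unadjusted testing, roughly 7 to 8 percentage points in the chance of at least one claim with 48 patients, and about 10 points with the 36 evaluable patients for whom the trial is sized, under the 0.4 SD assumption above.

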## 3. Discussion

The current work presents a design of a randomized controlled trial to assess tDCS effects on manual dexterity in MS patients. Patients will be randomly allocated to receive 3 tDCS blocks each constituted of 5 consecutive daily sessions of anodal motor tDCS, cathodal cerebellar tDCS, and sham over either cortical site. Each session will last 20 min, during which a current of 2mA in intensity will be delivered. This study design (i.e., protocol duration, session duration, and current intensity) was adapted from other studies where tDCS was applied in MS patients in the context of other symptoms [38,40]. So far, no randomized controlled trials have investigated the plausible tDCS effects on hand dexterity in MS patients. The choice of polarity was based on the results obtained following the application of repetitive transcranial magnetic stimulation (rTMS), which is another NIBS technique. High frequency rTMS applied over the motor cortex improved hand dexterity in MS subjects with cerebellar impairment possibly by increasing the motor cortex excitability [76,77]. In another study involving patients with essential tremor, low frequency rTMS applied over the cerebellum was able to improve the amplitude of tremor, a finding that might have occurred due to the decrease in excitability of the cerebellar cortex [78]. Following the same logic, anodal or cathodal tDCS could act by respectively increasing (i.e., anodal tDCS) or decreasing (i.e., cathodal tDCS) the cortical excitability of the stimulated areas [36,37]. This was behind the choice of using anodal tDCS aiming to increase the excitability of M1, and cathodal tDCS aiming to decrease the excitability of the cerebellar cortex in an attempt to release the inhibition exerted by the cerebellum over M1.

It is important to mention the various drawbacks that this study protocol might have. First, stimulation of the cerebellar cortex and/or M1 would also impact the lower limb functions, and evaluation of the balance and lower limbs’ motor power could provide additional information on the utility of such approaches. Secondly, we decided to adopt a previously tested setup that was designed to modulate the function of the entire cerebellar cortex; however, targeting the cerebellar cortex ipsilateral to the most affected site would be more efficient than bilateral cerebellar tDCS. Thirdly, although the assessment of long-term effects could help in the determination of the duration of tDCS effects, we thought of focusing our approach on the short-term effects given the exploratory nature of the study. Evaluation of long-term effects would be included in the upcoming research protocols.

## 4. Conclusions

Compared to rTMS, tDCS is portable and relatively simpler, cheaper, and could be fashioned into patient-administered home therapy [79]. This would make it of greater interest than rTMS if it proves its efficacy in this domain. The results of such a study might be promising for MS patients who suffer from altered manual dexterity and therefore may improve their quality of life. This work might also enhance the current understanding of the nature of cerebellar involvement in this clinical population [80]. Finally, regardless of the results, the study may contribute to develop a field that has not been explored yet.

## Figures and Tables

**Figure 1 brainsci-10-00185-f001:**
[figure not shown]
An illustration of a tDCS setup (Sooma Oy, Helsinki, Finland). a. Battery-driven stimulator. b. Anode. c. Cathode. * The reference electrode over the shoulder is not shown.

**Figure 2 brainsci-10-00185-f002:**
[figure not shown]
Flow chart of the study protocol.

**Figure 3 brainsci-10-00185-f003:**
[figure not shown]
The schematic diagram of the study protocol. 9-HPT: Nine-Hole Peg Test; CGI: Clinical Global Impression; CRQ: Comfort Rating Questionnaire; HADS: Hospital Anxiety and Depression Scale; MAS: Modified Ashworth scale; MFIS: Modified Fatigue Impact Scale; VAS*: Visual Analogue Scale for the pain recorded one week before and after the beginning of each block.
